#### Time and method of dreaming investigation

After emergence from sedation and orientation recovery, a modified Brice questionnaire was immediately used to evaluate the incidence of dreaming. Patients who reported dreaming were required to complete an awareness classification regarding the awareness level of their dreams.

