**Methods and analysis:**

This randomized, double-blind controlled trial to observe whether the generation of dreams is related to the dose of general anesthetics maintenance in the elective surgery under general anesthesia. A total of 124 participants will be randomly allocated to a low bispectral index or high bispectral index group at a ratio of 1:1. The Hospital Anxiety and Depression Scale (HADS) is used to assess the anxiety and depression status of participants during the perioperative period. Ramsay score is used to assess patients’ sedation level after surgery in the PACU. Modified Brice questionnaire and awareness classification are used to assess whether patients experienced dreaming during the surgery.

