## Introduction

Dreaming is a familiar and mysterious mode of cognitive function, and we involuntarily return to this mode every night. Dreaming during sleep is defined as “any type of cognitive activity that occurs during sleep” and is “a subjective experience that can only be obtained through the dreamer's memories after waking up.” Despite more than a century of scientific exploration, dreams continue to arouse the interest of sleep scientists, but they are still not fully understood [1, 2]. Moreover, its rigorous scientific exploration is a recent development, dating back to the discovery of rapid eye movement (REM) sleep in the 1950s. When this stage of sleep was first described in humans, researchers quickly noticed that people who awakened from REM sleep often reported dreaming (in 74% of cases, only 17% of non-REM [NREM] sleep). Therefore, dreaming is equivalent to rapid eye movement sleep, and this concept seems to be consistent with the electrophysiological characteristics of this sleep stage: closing the eyeballs under the eyelids, as if the sleeper is watching an animated scene [3, 4]. General anesthesia causes a drug-induced state of unconsciousness and is a non-physiological process that is similar to natural sleep. Its purpose is to create a state of sensory deprivation wherein patients are unresponsive to stimuli and thus leads to explicit amnesia [5]. Dreaming is also a common, long-lasting, and fascinating part of the anesthesia experience, but its cause and timing are still elusive. Patients usually report that they dreamed during anesthesia, but the actual time of dreaming during anesthesia is unknown. Dreaming during anesthesia can be defined as “any experience (excluding awareness) that a patient is able to recall and which he or she thinks occurred between induction of anaesthesia and the first moment of consciousness after anaesthesia” [6]. Patients receiving propofol for general anesthesia often report a higher incidence of dreaming compared with patients maintained with volatile anesthetics [7]. One explanation is that propofol and volatile anesthetics have different pharmacological effects in the central nervous system [8, 9]. Another explanation is that propofol can wake up from anesthesia faster than the volatile anesthetics, allowing patients to report their dreams before they are forgotten [10]. Why is the investigation of dreams during anesthesia important? Dreaming is one of the most common side effects of anesthesia, but it is still puzzling and requires explanation [7, 11]. Dreaming can sometimes make patients feel distressed and may reduce satisfaction with care [12]. Some patients who report dreaming worry that their anesthetic is insufficient; their experience is actually consciousness. At present, there is a hypothesis that dreaming occurs intraoperatively and is related to light or inadequate anesthesia; thus, in order to further verify the hypothesis, we choose elective surgery under general anesthesia to observe whether the generation of dreams is related to the dose of general anesthetics maintenance.

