#### Modified Brice questionnaire [16]

What was the last thing you remember before going to sleep?What was the first thing you remember from when you woke up?Can you recall anything between?Did you have any dreams while under anesthesia?How did you feel about your dream: pleasant, indifferent, or unpleasant?

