#### ***Awareness classification ***[17] 

No awareness: no reported awareness or a vague description, or what had been reported had a high probability of occurring in the immediate pre- or postoperative period; i.e., music, people talking, dressing applicationDreaming, possibly associated with awarenessPossible awareness: patient unable to recall any event definitely indicative of awarenessAwareness: recalled event was confirmed by attending personnel, or the investigators were convinced that the memory was real, but no confirmation could be obtained

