#### Safety assessment {22}

The anesthesiologist adjusted the intravenous speed of remifentanil and propofol according to hemodynamic parameters and BIS (BIS monitor; Aspect Medical System, Newton, MA). The BIS was maintained between 40 and 60 during the operation, which avoids the incidence of intraoperative awareness in patients in both groups.

During the study period, the adverse event record form is completed to record the duration, occurrence time, severity, measures, and outcome of the adverse event. The researchers will report it to the person in charge of the trial, the sponsoring unit, and the medical ethics committee in time. The ethics committee have the right to make the final decision if termination is needed.

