## Conclusion

In conclusion, the results of our trial are expected to demonstrate the proportion of patients in the HBIS group who had dreams during the surgery vs that of patients in the LBIS group and whether there are patient-reported awareness during anesthesia. Through all the patients who reported dreaming during the surgery, we are aimed to explore the proportion of those who reported having pleasant dreams in the LBIS group vs that of patients in the HBIS group, to further compare whether there is a difference in the dosage of propofol between the two groups, and to analyze the factors associated with different postoperative dream generation. In summary, according to the study results, we hope to provide a basis for good perioperative experience and better postoperative recovery of patients in clinical practice.

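### Awareness is classified only in patients who report a dream, so recall without a dream is elicited but has no stated route to classification

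*Protocol article*

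**What the plan says.** All places are in the protocol article.

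- **Time and method of dreaming investigation.** After orientation returns, "a modified Brice questionnaire was immediately used to evaluate the incidence of dreaming". No dreamers-only limit is put on this interview. The next sentence limits the second instrument: "Patients who reported dreaming were required to complete an awareness classification regarding the awareness level of their dreams".
- **Modified Brice questionnaire.** The third item, "Can you recall anything between", comes before the dream item and does not depend on it.
- **Awareness classification.** There are four categories. The lowest begins "No awareness: no reported awareness or a vague description". The highest is a recalled event that staff confirm or that the investigators believe to be real. Dreaming appears in one category only, the second.
- **Introduction.** Dreaming under anaesthesia is "any experience (excluding awareness) that a patient is able to recall", within a stated time window.
- **Conclusion.** Among the expected results is "whether there are patient-reported awareness during anesthesia".
- **Abstract, Methods and analysis.** "Modified Brice questionnaire and awareness classification are used to assess whether patients experienced dreaming during the surgery".
- **Safety assessment.** Keeping BIS within the range that spans both arms is described as something "which avoids the incidence of intraoperative awareness in patients in both groups".

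**The concern.** Entry to the awareness scale depends on the answer to a different question. By the protocol's own definition a dream is not awareness, so requiring a dream report first is a poor filter for finding awareness. The patient with recall and no dream has an answer that most needs grading, and the stated procedure does not grade it.

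Two things are at stake. First, awareness is a named result, and the arms differ in target BIS. A low classified count could reflect the filter and not the patients, and could then be read as support for the sentence in the Safety assessment. Second, the dream endpoint should match its definition. That requires a rule for dream reports that turn out to be awareness.

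**Working it through.** The protocol states no figure on this point, so there is none to reproduce. The check is a comparison of the text, followed by simple arithmetic on the size of the unclassified group.

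**Step 1. Follow each pattern of Brice answers through the stated procedure.**

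| Recall item | Dream item | Classified as written? | Category available on the scale? |
|---|---|---|---|
| no | no | no | yes, *No awareness* |
| no | yes | yes | yes |
| yes | yes | yes | yes |
| yes | no | **no** | yes, any category that needs no dream |

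The first row loses nothing of substance, because these patients would be placed in the lowest category. The fourth row is the gap. The scale has categories for these patients and the interview elicits the recall, but the rule does not connect the two.

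**Step 2. Size of the group outside the classification.** Inputs: 124 patients, 62 per group (Sample size), and a dream incidence *p* of 18% to 49.7% (Discussion, from earlier studies; assumed to apply here). Number not classified = 124 × (1 − *p*).

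- *p* = 0.18: 124 × 0.18 = 22.3 classified; 124 × 0.82 = 101.7 not classified (82%).
- *p* = 0.497: 124 × 0.497 = 61.6 classified; 124 × 0.503 = 62.4 not classified (50%).

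So about 22 to 62 patients would be classified (on average about 11 to 31 per arm) and about 62 to 102 would not. The unclassified group is the first and fourth rows of the table together. The documents do not say how it divides between them.

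**Step 3. Effect on a comparison between arms.** Let *a* be the true risk of awareness in an arm and *q* the probability that an aware patient also reports a dream. The expected classified count in that arm is 62 × *a* × *q*. The HBIS to LBIS ratio of classified counts is then (*a*_H × *q*_H) / (*a*_L × *q*_L). It equals the true ratio *a*_H / *a*_L only if *q* is the same in both arms. The trial exists to test whether dream reporting changes with depth of anaesthesia, so equal *q* cannot be taken for granted. The documents give neither *a* nor *q*, so neither the direction nor the size of the distortion can be derived.

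**Step 4. The dream count.** The Introduction excludes awareness from dreaming. The article does not say whether a dream report later graded *Awareness* stays in the dream count. The abstract's sentence on the two instruments is compatible with using the classification to take such reports out. The text therefore leaves a rule to be aligned with the definition; it does not state a wrong one.

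**The case against.** The strongest reply is that the filter loses little. The Brice interview carries no dreamers-only limit and its recall item comes before the dream item. The Conclusion promises only to say whether patient-reported awareness occurred, and the recall item can go some way to answering that without a four-level scale. The classification is described as grading the dreams, a legitimate if narrow purpose. Dreaming, not awareness, is the trial's question, and the filter changes neither who is asked about dreams nor the sample size.

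Much of this stands, and it rules out several stronger readings that a reader might infer:

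- *Awareness without a dream is never counted, or is certain to be missed.* The recall item elicits it. What is missing is grading and confirmation.
- *The article promises awareness by arm.* The Conclusion writes out the comparison of arms for dreams and for pleasant dreams. For awareness it says only whether any is reported. A comparison by arm is a natural reading but is not explicit.
- *The 62 to 102 unclassified patients are missed awareness cases.* They are expected non-dreamers, and presumably most have nothing to classify.
- *Dream reports graded as awareness stay in the dream count.* The article does not say so, and the abstract leaves room for the opposite.
- *Patients grade their own awareness.* That rests on one loose verb. The blinding section gives outcome assessment to a second, blinded anaesthesiologist, and the top category plainly calls for staff or investigator judgement.
- *The Safety assessment sentence is a hypothesis that the scale is meant to test.* It reads as a rationale for the BIS range.

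What the reply does not remove is the fourth row of the table. The restriction is a rule the article states, not a detail left to a fuller document, and it does not fit the article's own definition, its scale or its named result. The adverse event form in the Safety assessment is not limited to dreamers, but it does not name awareness and is not linked to the scale.

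**Conclusion.** The point holds in a limited form. Followed as written, the procedure elicits recall without a dream but gives it no route to classification or confirmation. Classified awareness is therefore incomplete and conditional on a post-randomisation outcome that may differ by arm.

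The number of affected patients cannot be derived from the documents and may be small. The range of about 62 to 102 of 124 is only the size of the group outside the classification, and it assumes that the cited 18% to 49.7% carries over to this trial. The conclusion also assumes that the Brice interview was given to all patients; the text implies this by setting no limit but does not state it.

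**What to change.** 1. Have the existing blinded outcome assessor apply the awareness classification to every interviewed patient from the recorded Brice answers. Any recall on the third item or any dream on the fourth leads to grading; all other interviewed patients are placed in *No awareness*.
2. Report *Possible awareness* and *Awareness* by group, separately from dreaming, with all randomised patients as the denominator. State the number not interviewed, if any.
3. Apply the Introduction's definition to the endpoint: reports graded *Awareness* are not counted as dreams in the main analysis. Add a sensitivity count that includes them.
4. Complete the grading before the allocation is opened, which the article places at the time of data analysis.

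The cost is a wording change and a few minutes of assessor time per record, with no new patient contact. Trial status reports recruitment finished and data collection in progress, so the change depends on the Brice answers, including the content of any recall, having been stored. Staff confirmation may be harder to obtain for interviews already done. The top category also allows the investigators' judgement without confirmation, so these records can still be graded, and the report should say which were confirmed.

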#### Modified Brice questionnaire [16]

What was the last thing you remember before going to sleep?What was the first thing you remember from when you woke up?Can you recall anything between?Did you have any dreams while under anesthesia?How did you feel about your dream: pleasant, indifferent, or unpleasant?

#### ***Awareness classification ***[17] 

No awareness: no reported awareness or a vague description, or what had been reported had a high probability of occurring in the immediate pre- or postoperative period; i.e., music, people talking, dressing applicationDreaming, possibly associated with awarenessPossible awareness: patient unable to recall any event definitely indicative of awarenessAwareness: recalled event was confirmed by attending personnel, or the investigators were convinced that the memory was real, but no confirmation could be obtained

#### Strategies to improve adherence to interventions {11c}

The investigators will explain the treatment intervention in detail and supervise the compliance of the intervention throughout the entire procedure (during maintenance of anesthesia). Periodic monitoring will be conducted by a blinded investigators, for the recording of postoperative parameters and to ensure adherence to interventions.

#### Relevant concomitant care permitted or prohibited during the trial {11d}

Usual induction of anesthesia is permitted for both intervention and control groups. Adverse effects such as hypotension, bradycardia, nausea and vomiting, and hypoxemia were also treated accordingly. Participation in additional research trials is prohibited during the trial.

#### Safety assessment {22}

The anesthesiologist adjusted the intravenous speed of remifentanil and propofol according to hemodynamic parameters and BIS (BIS monitor; Aspect Medical System, Newton, MA). The BIS was maintained between 40 and 60 during the operation, which avoids the incidence of intraoperative awareness in patients in both groups.

During the study period, the adverse event record form is completed to record the duration, occurrence time, severity, measures, and outcome of the adverse event. The researchers will report it to the person in charge of the trial, the sponsoring unit, and the medical ethics committee in time. The ethics committee have the right to make the final decision if termination is needed.

#### Provisions for post-trial care {30}

There is no anticipated harm and compensation for trial participation.

#### Procedure for unblinding if needed {17b}

At the end of the study, the original data and results will be submitted to the scientific research management committee, and they will be disclosed to the public after the results are published.

#### Plans to promote participant retention and complete follow-up {18b}

Full communication before surgery, in order to dispel the patient’s fear; explanation of the specific situation to establish trust between doctors and patients; and obtaining of informed consent were performed. A verbal explanation of the written consent will be provided by the research member, and any questions regarding the study will be answered. Each participant will have sufficient time to decide whether to participate in this study. If patients are willing to participate, written consent will be obtained.

#### Data management {19, 27}

All personal information about the participants will be collected and stored in a secure cabinet by the lead investigators, throughout the duration of the study, to guarantee confidentiality. Only the lead investigator will have access to the files corresponding to the personal data of the participants.

#### Protocol amendments {25}

The study plan of this project has been registered with approval number 2021PS664K. If any changes to the protocol are required, we will first notify the sponsor and funder; then, the principal investigator (PI) will notify the center, and a copy of the revised protocol will be sent to the PI for addition to the investigator site file. Any deviation from the agreement will be fully documented using the violation reporting form. The PI for this study will update the protocol in the Clinical Trials Registry.

### Statistical analysis

#### Sample size

In this trial, according to the previous study [18], the total dose of propofol in the dream group was 337 ± 161 mg and by 259 ± 145 mg in the no dream group. Using a *t* test of two independent samples in PASS for calculation, the withdrawal rate is 20% to ensure that the results are statistically different (*α* = 0.05, 1-*β* = 0.8); therefore, each group requires 56 subjects. To improve the reliability of the trial, we will recruit a total of 124 patients, with 62 in each group.

The SPSS 20.0 statistical software (SPSS, Inc., Chicago, IL, USA) and GraphPad Prism 6.0 software were used for data analysis. Continuous data were tested for normality. Normally distributed data were summarized using mean and standard deviation and were compared using unpaired two-tailed *t*-tests. Skewed data were summarized using.median and range and were compared using Wilcoxon rank-sum tests. Categorical data were summarized using number (%) and were compared using *Χ*^2^ test or Fisher’sexact tests. Logistic regression was used to determine predictors of dreaming and correlation with dream quality. Categorical variables were created from continuous variables in applicable cases. A *P* value of less than 0.05 was considered statistically significant.

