## Discussion

Dreams are a remarkable experiment in psychology and neuroscience, conducted every night in every sleeping person. They show that the human brain, disconnected from the environment, can generate an entire world of conscious experiences by itself. The occurrence of dreams is also one of the common phenomena of anesthesia and sedation. The occurrence of dreams during general anesthesia has been reported in the literature. The dream after anesthesia refers to the patient’s experience after the induction of anesthesia to the beginning of the waking phase. Domestic scholars have conducted research on the effects of short-town intravenous anesthesia and specific anesthetics on dreams of adult receiving surgery, which found that the incidence of adult dreams is about 18% ~ 49.7% [19, 20]. Among them, different anesthesia drugs, operation site, operation time, and so on are all the influential factors leading to the occurrence of dreams. Previous hypothesis also thought that dreaming occurs intraoperatively and is related to light or inadequate anesthesia [21, 22]. In order to verify this previous hypothesis, we designed a randomized, observer- and patient-blinded, controlled clinical trial, which compared the effects of different maintenance doses of propofol on patients’ dreams and analyzed the related factors affecting dreams. A recent study has shown that depression and anxiety assessed by Beck anxiety/depression inventory can predict a negative dream during natural sleep [23]. Similarly, we assessed preoperative anxiety level to see if patients with different preoperative anxiety states were associated with different dreams generated during anesthesia. In our trial, the subjective outcomes including HADS, Ramsay scale, modified Brice questionnaire, and awareness classification will be assessed. In this way, the effect of different dose of propofol maintained during the surgery on the incidence of dreaming of patients will be evaluated from multiple perspectives.

Our study has some limitations. First, since all the patients were hospitalized, we only scored the preoperative anxiety during the perioperative period but did not evaluate the daily long-term psychological base state and the degree of dreaming under natural sleep. Second, the study was part of a single-center survey, multicenter survey still need to be studied.

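### The 80% power is calculated for propofol dose in dreamers versus non-dreamers, so it is not established for the randomised comparison of dreaming incidence between HBIS and LBIS

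*Protocol article*

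**What the plan says.** The Sample size section of the protocol article cites a previous study in which "the total dose of propofol in the dream group was 337 ± 161 mg and by 259 ± 145 mg" among those who did not dream. It enters these figures into a two-independent-sample t test with α = 0.05 and power 0.8, mentions 20% withdrawal, and arrives at 56 per group. This is raised to 62 per group, 124 in total.

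The groups of 62 are the randomised arms: the Randomization section allocates 62 to LBIS (BIS 40–50) and 62 to HBIS (BIS 50–60).

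The idea under test is that "dreaming occurs intraoperatively and is related to light or inadequate anesthesia". The Conclusion puts first, among the results expected, "the proportion of patients in the HBIS group who had dreams during the surgery vs that of patients in the LBIS group". That outcome is binary, and the Statistical analysis section assigns categorical data to a chi-square or Fisher's exact test. The article gives no expected dreaming rate for either arm and no target difference. The only rate is in the Discussion, from earlier work in adults: "the incidence of adult dreams is about 18% ~ 49.7" per cent.

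**The concern.** Three elements of the calculation do not match the randomised question. The variable is total milligrams of propofol, not dreaming. The groups are dreamers and non-dreamers, which arise after randomisation and cannot be fixed at 62 each. The test is a t test, whereas the arm comparison of dreaming uses chi-square or Fisher.

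At stake is how a non-significant result is read. A reader who sees 80% power next to 62 per group may take a null arm comparison as an adequately powered negative. The article gives no basis for that, because it never says what difference in dreaming incidence the trial was sized to find.

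**Working it through.** **1. The plan's own figure.** Inputs from the Sample size section: difference 337 − 259 = 78 mg; SDs 161 and 145; α = 0.05; power 0.80; withdrawal 20%. The sample-size sentence does not state sidedness; two-sided is used here, as in the planned t tests.

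n per group = (1.960 + 0.842)² × (161² + 145²) / 78² = 7.849 × 46,946 / 6,084 = 60.6, so 61 (62 with the t distribution). Dividing by 0.8 for withdrawal gives 77–78. The stated 56 is not reproduced from the full inputs. A figure of 55–56 appears if SD 145 is used for both groups with no allowance for withdrawal. This is a side observation; the point does not depend on it.

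**2. Power of the dose contrast with realistic splits.** The calculation assumes equal numbers of dreamers and non-dreamers. Taking 18%, 30% and 49.7% dreaming among 124 (18% and 49.7% from the Discussion; 30% is an assumed middle value), with SE = √(161²/n₁ + 145²/n₀) and a two-sided Welch t test:

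| Dreamers : non-dreamers | SE (mg) | 78/SE | Power |
|---|---|---|---|
| 22 : 102 | 37.2 | 2.10 | 53% |
| 37 : 87 | 30.7 | 2.54 | 71% |
| 62 : 62 | 27.5 | 2.83 | 80% |
| 18 : 81 (20% lost) | 41.2 | 1.89 | 44% |
| 50 : 50 (20% lost) | 30.6 | 2.55 | 71% |

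The 80% therefore needs about half of the patients to dream and no losses. The low end varies a little with the method: a normal approximation gives 56% where Welch gives 53%.

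**3. Power of the randomised comparison.** No rate by arm is given, so the rates below are assumptions. Lower-arm rates of 18% and 49.7% are the ends of the Discussion's range; 30% and 40% lie between. Two-sided 0.05, pooled-variance test of two proportions:

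power = Φ{ [ |p₂ − p₁| − 1.960 √(2p̄(1 − p̄)/n) ] / √( [p₁(1 − p₁) + p₂(1 − p₂)]/n ) }, with p̄ = (p₁ + p₂)/2.

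The higher rate needed for 80% power:

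| Lower rate | 62 per arm | 50 per arm (62 × 0.8 = 49.6) |
|---|---|---|
| 18% | 40.7% (22.7 points) | 43.6% (25.6) |
| 30% | 54.6% (24.6) | 57.5% (27.5) |
| 40% | 64.9% (24.9) | 67.6% (27.6) |
| 49.7% | 73.9% (24.2) | 76.4% (26.7) |

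Power for given differences:

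| Contrast | 62 per arm | 50 per arm |
|---|---|---|
| 18% v 28% | 26% | 22% |
| 18% v 33% | 48% | 40% |
| 30% v 45% | 41% | 34% |
| 18% v 49.7% | 97% | 93% |

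Depending on the true rates, power for the arm comparison thus runs from about a quarter to nearly certain. The article's 80% identifies no point on that scale.

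**The case against.** The strongest reply is that a link between dose and dreaming is a declared aim. The Abstract and Introduction ask whether dreaming is related to the maintenance dose, the analysis section plans logistic regression for predictors of dreaming, and the Conclusion lists a comparison of propofol dosage between the arms. This stands in part: the calculation does serve a stated aim, though a non-randomised one. It does not carry over to the arms. The 337 and 259 mg are dreamers and non-dreamers, and the article gives no expected LBIS–HBIS difference in dose.

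The 20% withdrawal scenario may also be pessimistic. Dreaming is assessed immediately after orientation returns, and the missing-data section expects no missing postoperative data. That is why results are shown at both 62 and 50 per arm.

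Two stronger readings are tempting and are not supported:

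- A reader might infer that the planning figures contradict the hypothesis, since dreamers received more propofol while the hypothesis concerns light anaesthesia. Total milligrams also reflect how long the infusion ran, and the Discussion itself names operation time as an influence on dreaming. The figures do not show which patients were more deeply anaesthetised.
- A reader might infer that the trial is underpowered outright. The article states no clinically relevant difference and no rate by arm, and 18% v 49.7% would be detected with 97% power at 62 per arm.

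**Conclusion.** The concern holds in this form: the stated 80% power is not established for the randomised comparison of dreaming incidence. For the dose contrast it holds only with a near-even split of dreamers and no losses (53–80% across the article's incidence range with all 124 patients, about 44–71% after 20% withdrawal). For the arm comparison, 124 patients give 80% power for about 23–25 points, or about 26–28 points at 50 per arm.

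These figures rest on assumed rates within the article's 18–49.7% range, two-sided 0.05 and a pooled-variance test. The article labels no primary outcome, and a full protocol not shown may do so. That dreaming by BIS arm is the randomised question is taken from the title, the Discussion and the Conclusion.

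**What to change.** Trial status says recruitment is finished, so N stands and what it delivers should be restated. In a dated amendment made before unblinding:

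- Keep the dose-based calculation as the historical basis for N, and state that it does not give the power of the arm comparison.
- Identify the proportion reporting a dream (the dream item of the modified Brice questionnaire) in HBIS versus LBIS as the randomised comparison of primary interest. This must agree with any earlier designation, or be declared as made late.
- State what N delivers, with the rates labelled as assumptions from the 18–49.7% range: at two-sided 0.05, 80% power for about 23–25 points at 62 per arm or 26–28 at 50 per arm; at 62 per arm, about 48% and 41% power for 15 points from 18% and 30%, and 97% for 18% v 49.7%.
- Report the risk difference with its 95% CI, so that a null result is not read as no effect.

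The cost is wording and a less favourable power statement. No extra patients are needed, and the planned chi-square or Fisher test is unchanged.

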## Abstract

**Introduction:**

Dreaming reported after anesthesia remains a poorly understood phenomenon. At present, there is a hypothesis that dreaming occurs intraoperatively and is related to light or inadequate anesthesia; thus, in order to further verify the hypothesis, we choose elective surgery under general anesthesia to observe whether the generation of dreams is related to the dose of general anesthetics maintenance.

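### The 80% power stated for propofol dose in dreamers v non-dreamers assumes equal groups, which randomisation cannot provide; at 18% dreaming it is about 53-60% with all 124 patients evaluable

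*Protocol article*

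**What the plan says.** The Sample size section rests on one earlier study, in which "the total dose of propofol in the dream group was 337 ± 161 mg and by 259 ± 145 mg in the no dream group". It names a "test of two independent samples in PASS for calculation", with alpha 0.05, power 0.8 and 20% withdrawal, and concludes "therefore, each group requires 56 subjects". It then sets recruitment at 124, 62 per group.

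The groups allocated 1:1 are the two BIS arms (abstract, Methods and analysis; Randomization, study intervention, and blinding). Dreaming is established by the modified Brice questionnaire after the patient has emerged and is orientated (Time and method of dreaming investigation). The Discussion, citing earlier work, reports that "the incidence of adult dreams is about 18% ~ 49.7" per cent. The abstract gives the aim as to "observe whether the generation of dreams is related to the dose of general anesthetics maintenance".

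**The concern.** The inputs describe patients classified by an outcome. The investigator can fix how many patients enter the low-BIS and high-BIS arms, but not how many will report a dream. A single required number for each group is the equal-allocation form of the t-test calculation. For dreamers and non-dreamers it is met only if about half of the patients dream, which is the very top of the range that the article quotes. The section mentions no unequal split.

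The only power figure in the article is attached to this dose-by-dreaming contrast, and the stated aim is about dose and dreaming. If few patients dream, a real 78 mg difference is missed more often than the 20% that the section implies, and a null result could be read as coming from an 80%-powered comparison. A second, smaller effect is that the group likely to be smaller has the larger SD (161 v 145), so a pooled t test understates the standard error.

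**Working it through.** **Inputs.** Means 337 and 259 mg (difference 78), SDs 161 and 145, alpha 0.05, 20% withdrawal and N = 124, all from Sample size; two-tailed t tests from Statistical analysis (the sample-size sentence gives no sidedness); incidence 18% to 49.7% from the Discussion. The 30%, 34% and 40% rows are points that I chose inside that range.

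**1. The plan's own figure.** Root-mean-square SD = √((161² + 145²)/2) = 153.2, so the standardised difference is 78/153.2 = 0.509. With a normal approximation, n per group = 2 × (1.960 + 0.842)² × 153.2²/78² = 61; the t test needs 62. Allowing for 20% withdrawal, 62/0.8 gives 78. The stated 56 is not reproduced: at 56 v 56 power is 76.1%. That is a separate matter. I therefore start from the 124 recruited, where an equal 62 v 62 split gives 80.3%. Any drop below that at N = 124 comes from imbalance alone.

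**2. Group sizes.** Dreamers = N × incidence, rounded. For 124: 0.18 × 124 = 22, leaving 102; 0.30 × 124 = 37, leaving 87; 0.40 × 124 = 50, leaving 74; 0.497 × 124 = 62, leaving 62. After withdrawal, 0.8 × 124 = 99.

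**3. Standard error of the difference**, √(161²/n₁ + 145²/n₂):
- 62 v 62: √(418.1 + 339.1) = 27.5 mg; 78/27.5 = 2.83
- 22 v 102: √(1178.2 + 206.1) = 37.2 mg; 78/37.2 = 2.10

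At 22 v 102 the Welch degrees of freedom are about 29 and the critical value 2.05, so a signal of 2.10 standard errors gives power of 52.6%.

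**4. Power over the range** (Welch from the noncentral t; pooled t by simulation with the stated unequal SDs):

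| Dreaming | 124 evaluable: split | Pooled / Welch | 99 evaluable: split | Pooled / Welch |
|---|---|---|---|---|
| 18% | 22 v 102 | 60% / 53% | 18 v 81 | 52% / 44% |
| 30% | 37 v 87 | 74% / 71% | 30 v 69 | 65% / 61% |
| 34% (midpoint) | 42 v 82 | 76% / 74% | not tabulated | not tabulated |
| 40% | 50 v 74 | 79% / 78% | 40 v 59 | 70% / 68% |
| 49.7% | 62 v 62 | 80% / 80% | 49 v 50 | 71% / 71% |

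If the calculation was meant to be one-sided, power at 18% with 124 evaluable would be about 66% to 70%, still short of 80%.

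**5. Type I error of the pooled test at 22 v 102.** Pooled SD = √((21 × 161² + 101 × 145²)/122) = 147.9, giving an SE of 147.9 × √(1/22 + 1/102) = 34.8 mg against the true 37.2 mg. The effective cut-off is 1.98 × 34.8/37.2 = 1.85 standard errors, a two-sided error of roughly 6.5%; simulation gives about 6.7%. Welch stays near 5%.

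**The case against.** The strongest reply is that the word group in this section means LBIS and HBIS: the section ends with 62 per group, which is how the arms are described, and the Conclusion lists between-arm comparisons. On that reading the split is 1:1 by design. It does not rescue the power statement, because doses in dreamers and non-dreamers are then the wrong inputs for the arms. It does show that the figures above must not be passed off as the power for LBIS v HBIS, and a reader might infer that the randomised comparison has only 53-60% power. Nothing here supports that: the calculation does not address that contrast.

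Second, the 18% to 49.7% range is background literature, not a design assumption, and the Discussion says that incidence varies with drug, site and duration. The Introduction also reports more dreaming with propofol, which both arms receive. This stands: 18% is a possibility, not a forecast. But it belongs to the only range given, and the equal split is itself an unstated assumption of about 50%.

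Third, a reader might infer that power is far below 80% over most of the range. With 124 evaluable it is not: 74-76% at the midpoint and 78-79% at 40%.

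Fourth, no dream v no-dream t test is explicitly planned; the method named for predictors of dreaming is logistic regression. So the Welch advice is conditional. The SDs are also close (variance ratio 161²/145² = 1.23), and the type I inflation is correspondingly modest.

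Finally, the section on missing data expects no missing postoperative data, so 99 evaluable may be pessimistic. It is nevertheless the plan's own withdrawal allowance.

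**Conclusion.** The point holds as a power statement that the design cannot guarantee for the comparison from which it was derived. With all 124 evaluable, imbalance alone lowers power from 80% to about 60% pooled or 53% Welch at 18% dreaming, and to 74% or 71% at 30%. From 40% upwards the loss is one or two percentage points. With 99 evaluable, 80% is not reached at any incidence in the quoted range, but there part of the shortfall is withdrawal: even a near-equal split gives 71%.

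This rests on the stated means and SDs carrying over to this trial, approximately normal doses, a two-sided 5% test, and the literature range for incidence. The BIS targets may themselves change the spread of total dose, which the documents do not quantify. The consequence is an overstated power claim; it does not invalidate the trial.

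**What to change.** Recruitment is reported as finished (Trial status), so no extra patients are proposed. In Sample size, replace the equal-group 80% statement for dose by dreaming with power at the unequal splits, for both 124 and 99 evaluable patients. Suggested wording: For the non-randomised comparison of propofol dose between patients who do and do not report dreaming, assuming 337 ± 161 v 259 ± 145 mg and two-sided alpha 0.05, power (Welch test) is about 53%, 71%, 78% and 80% at 18%, 30%, 40% and 49.7% dreaming with 124 evaluable patients, and about 44%, 61%, 68% and 71% with 99. These figures are not the power for LBIS v HBIS.

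If dream v no-dream dose is compared by t test, name the unequal-variance (Welch) version.

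Cost: wording only, with no new data. The downside is that the stated power becomes less favourable, and at low incidence Welch shows less power than the pooled test, part of whose apparent advantage is its inflated type I error.
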